#### Maternal outcomes

Gestational hypertension: development of new-onset hypertension (blood pressure persistently ≥ 140/90 mmHg on two occasions at least 4 h apart during pregnancy after 20 weeks of gestation, labor, or the puerperium in previously normotensive nonproteinuric womenPreeclampsia: gestational hypertension with proteinuriaGestational proteinuria: spot urine for initial estimation of total protein excretion of 300 mg or more/24 hGestational diabetes: using a 75-g 2-h oral glucose tolerance test, any of the fasting glucose ≥ 5.1 mmol/L, 1-h plasma glucose ≥ 10 mmol/L, or 2-h plasma glucose ≥ 8.5 mmol/LAntepartum hemorrhage: any vaginal bleeding during pregnancy from 24 weeks to termNauseaVomitingSerum progesterone level at recruitment, between 18 + 0 and 23 + 6 weeks and between 28 + 0 and 31 + 6 weeks

#### Neonatal outcomes

Birth weightApgar scoreSmall for gestational age (<10th percentile for birth weight)Head circumference: measure at the occipital frontal levelCongenital anomalyNeonatal intensive care unit admissionIntraventricular hemorrhage, diagnosed by ultrasound scan
▪ Grade 1: germinal matrix hemorrhage only or germinal matrix hemorrhage plus intraventricular hemorrhage < 10% of ventricular area▪ Grade 2: intraventricular hemorrhage, 10–50% of ventricular area▪ Grade 3: intraventricular hemorrhage involving > 50% of ventricular area; lateral ventricles are usually distended▪ Grade 4: parenchymal bleed in any locationSevere intraventricular hemorrhage (grade 3 or 4 periventricular-intraventricular hemorrhage)Cystic periventricular leukomalaciaNecrotizing enterocolitis above stage 1, defined by modified Bell staging criteria as stage IIA or aboveBronchopulmonary dysplasiaRespiratory distress syndrome (radiological evidence of respiratory distress syndrome)Severe retinopathy of prematurity (stage 3 ROP retinopathy of prematurity or higher)Proven sepsisIn-hospital deathLength of stayHemodynamically significant patent ductus arteriosus requiring ligation

### Statistics

#### Statistical tests

##### Analysis plan

All statistical analyses will be carried out using SAS version 9.2 or above (SAS Institute, Cary, NC, USA) and/or R version 3.2.0 or above (R Foundation for Statistical Computing, Vienna, Austria) or IBM SPSS Statistics software (IBM, Armonk, NY, USA).

The primary analysis will be evaluated by Fisher’s exact test to compare the difference of PTB rates between the progesterone and control groups. The analysis will primarily be carried out according to intention-to-treat and per-protocol principles. The intention-to-treat analysis will include any randomized subjects with nonmissing primary outcome data. The per-protocol analysis will include all randomized subjects in the intention-to-treat analysis who have sufficient treatment compliance (≥ 80%) and no major protocol deviations.

Nominal data will be described by frequencies and percentages, and correlations will be analyzed using the chi-square test; continuous data will be expressed as mean ± standard deviation or median (range) and analyzed using Student’s *t* test or the Mann-Whitney *U* test, depending on the normality of the data. Logistic regression analysis will be applied to evaluate the association between PTB and the effect of early universal use of progesterone, history of previous PTB, cervical length measurement at 18 + 0 to 23 + 6 weeks of gestation, serum progesterone level, and other risk factors, if appropriate. The interaction effect will be evaluated to assess the impact of the history of previous PTB or cervical length on treatment effect. A *P* value < 0.05 will be considered as statistically significant. Interim analysis will be done when the primary outcome is available for 850 subjects (~ 50% of the intended recruitment), and the trial will be stopped if there is a significant difference in the PTB rate between the two groups.

The research assistants will be responsible for data entry. Hard copies will be locked in a cabinet during the course of the study, and the electronic copy will be encrypted/password-protected. The data collected during the course of the research will be kept strictly confidential and will be accessible only by members of the trial team. Anonymized trial data can be shared with other researchers to enable international meta-analyses.

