**Methods:**

This is a multicenter, randomized, double-blind, placebo-controlled trial registered with ClinicalTrials.gov on 12 February 2018. Eligible consecutive pregnant women with singleton gestation attending antenatal outpatient clinics will be recruited after receiving counseling and signing the written consent form. Transvaginal cervical length measurement will be performed at recruitment (before 14 + 0 weeks of gestation) and between 18 + 0 and 23 + 6 weeks of gestation. After randomization, women will be randomly assigned to either the treatment group (oral dydrogesterone 10 mg three times daily) or the placebo group, and medication will be started before 14 + 0 weeks of gestation. Assigned groups will be unblinded if the cervical length is ≤ 25 mm between 18 + 0 and 23 + 6 weeks of gestation, and the management option for short cervix will be discussed (oral progesterone, vaginal progesterone, or cervical cerclage). The primary outcome is preterm birth before 37 + 0 weeks of gestation.

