Progesterone, by its maintenance of uterine quiescence through anti-inflammatory effects, has been shown to decrease the risk of PTB in women with the aforementioned risk factors [11, 12]. In women with prior PTB, the weekly use of 250 mg of 17α-hydroxyprogesterone caproate intramuscularly could reduce the PTB rate before 37 weeks of gestation from 54.9% to 36.3% (relative risk [RR], 0.66; 95% confidence interval [CI], 0.54–0.81) [11]. In women with asymptomatic short cervix (TVCL measurement of 10–20 mm) at the second trimester, 90 mg of vaginal progesterone could effectively reduce PTB before 33 weeks from 16.1% to 8.9% (RR, 0.55; 95% CI, 0.33–0.92) [13]. Universal cervical length screening followed by treatment with vaginal progesterone has been shown to be the most cost-effective strategy for preventing PTB [14, 15]. These findings were confirmed in a meta-analysis [16].

Nevertheless, only a minority of women may benefit from progesterone treatment if it is started at the second trimester. This is because only approximately 10% of spontaneous early PTB cases were associated with a history of prior PTB [17] and approximately 5% of women had a cervical length of approximately 20 mm at 22 + 0–24 + 6 weeks of gestation [7]. Therefore, the remaining women who may have PTB may not have any identifiable risk factor. Even if physicians are able to detect these risk factors and offer progesterone treatment at approximately 16–24 weeks, 36.3% of women with a history of PTB and 30.2% of women with an asymptomatic short cervix still give birth before 37 weeks [11, 13]. There is still a large proportion of PTB, which is currently not preventable, and the current approach to preventing PTB is far from ideal. One possible hypothesis is that the initiation of progesterone treatment would be too late for its effect to take place. Early progesterone treatment may maintain uterine quiescence and prevent shortening of the cervix from early gestation [18].

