### Objectives and hypothesis

#### Primary objective

The aim of this multicenter, randomized, double-blind, placebo-controlled trial is to determine whether early universal use of oral progesterone before 14 + 0 weeks of gestation can prevent PTB in singleton gestations better than universal screening of cervical length at 18 + 0 to 23 + 6 weeks of gestation, followed by progesterone treatment in those with a short cervix in a singleton pregnancy. The hypothesis is that early universal progesterone treatment from before 14 + 0 weeks could decrease the risk of PTB further than progesterone treatment in women with an asymptomatic short cervix detected by universal cervical length screening.

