### Randomization and masking

The randomization process will be done in a 1:1 ratio by a research nurse not involved in the women’s clinical care, using a computer program. The result of each randomized participant will be put in a sequentially numbered, opaque, sealed envelope. One envelope will be opened if a woman agrees to join the study. Women will be randomly assigned at the time of recruitment to one of the two groups on the day of first TVCL measurement before 14 + 0 weeks of gestation:
*Treatment group*: dydrogesterone 10 mg three times daily (Abbott Biologicals B.V., Olst, The Netherlands)*Placebo group*: placebo identical to the active drug in external appearance but without an active ingredient

Participating women, attending clinicians, study investigators, and study coordinators are blinded to the group assigned.

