### Procedure

Ultrasonographers must attend the “Cervical Assessment” online lecture and obtain the certificate of competence from the Fetal Medicine Foundation website. TVCL will be measured using a standard protocol [19]. Women will be asked to empty the urinary bladder before the TVCL measurement. A transvaginal ultrasound probe will be inserted into the vagina and directed into the anterior fornix. A sagittal view of the cervical canal will be obtained, and excessive pressure on the cervix will be avoided. Cervical length will be defined as the linear measurement of the cervical canal between the V-shaped internal and external os, surrounded by the hypoechoic endocervical mucosa. The shortest distance between the three measurements will be recorded. If uterine contraction is observed in the lower segment close to the internal os, ultrasound will be repeated after 5–10 min when the contraction ceases. After the baseline cervical length assessment, women will be instructed to take the oral progesterone or placebo accordingly, three times per day, from 12 + 0 to 14 + 0 weeks to 36+ weeks of gestation.

A second TVCL assessment will be performed between 18 + 0 weeks and 23 + 6 weeks of gestation. On the basis of available evidence of progesterone treatment in women with asymptomatic short cervix [12], women in the assigned group will be unblinded if the TVCL measurement is ≤ 25 mm. The women receiving placebo will be given the option of oral progesterone (10 mg three times per day) or vaginal progesterone 200 mg daily (Endometrin, Ferring Pharmaceuticals Inc., Parsippany, NJ, USA; or Utrogestan, Besins Healthcare, Monaco) until 36+ weeks of gestation (or cervical cerclage if the women has a history of preterm delivery or second-trimester miscarriage) [20]. For women in the progesterone group whose cervical length is ≤ 25 mm at 18 + 0 to 23 + 6 weeks of gestation, options will be offered of continuation of oral progesterone (10 mg three times per day), vaginal progesterone 200 mg daily (Endometrin or Utrogestan), or cervical cerclage if the women have a history of PTB.

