#### Sample size estimation

The PTB rate of singleton pregnancy at 37 weeks of gestation in Hong Kong is approximately 6.5% [21]. Among the local population, 4.6% had cervical length < 25 mm [22]. The use of universal screening of cervical length followed by treatment with vaginal progesterone in those with a short cervix would further bring down the rate to 6% [23]. Treatment with progesterone is anticipated to further reduce this proportion by an absolute difference of 3%. A sample size of 814 per group is required to achieve power of 80% power at the 5% significant level based on Fisher’s exact test. Assuming an attrition rate of 5%, a total of 1714 subjects (857 subjects per group) will be recruited.

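### Mid-trimester cervical length is compared without adjustment for the baseline cervical length planned for every woman: a valid analysis, but less precise than it could be at no cost

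*Protocol article*

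**What the plan says.** All references are to the Protocol article.

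- **Outcome.** The Obstetric outcomes list has nine secondary items. One is the cervical length found at the second scan, in the window in which the Primary objective places universal screening of "cervical length at 18 + 0 to 23 + 6 weeks".
- **Analysis rule.** Under Analysis plan, "continuous data will be expressed as mean ± standard deviation or median (range) and analyzed using" a two-group test, either Student's t or Mann-Whitney U according to normality. No covariate is mentioned, and no continuous outcome is treated differently.
- **Baseline value.** The Abstract (Methods) states "Transvaginal cervical length measurement will be performed at recruitment (before 14 + 0 weeks of gestation" and again at the mid-trimester scan. Under Randomization and masking, women are assigned "on the day of first TVCL measurement before 14 + 0 weeks of gestation". Under Procedure, "After the baseline cervical length assessment, women will be instructed to take the oral progesterone or placebo accordingly". The first measurement is therefore planned for all women and comes before treatment.
- **The only regression.** "Logistic regression analysis will be applied to evaluate the association between PTB and the effect of early universal use of progesterone", together with prior preterm birth, mid-trimester cervical length, serum progesterone and other risk factors. Its response is preterm birth; cervical length appears only as an explanatory variable.
- **Link to the mechanism.** Background and rationale offers, as one possible hypothesis, that "Early progesterone treatment may maintain uterine quiescence and prevent shortening of the cervix from early gestation".

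**The concern.** Shortening is a change from an early value, and the trial measures that early value in every woman with the same technique and before any drug. A two-group test of the later value alone leaves in the error term all the variation that a woman's starting length could explain. If the two scans are correlated, the comparison has a wider confidence interval than the collected data allow.

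What is at stake is the precision of one secondary comparison that bears on how early progesterone might act. The method is stated in the document, so this is a choice that can be improved and not a detail left to another document.

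**Working it through.** **1. The plan's own figure.** The document gives no standard deviation, target difference or power for cervical length, so the only figure to reproduce is the sample size for preterm birth. Inputs from Sample size estimation: control rate 6% (screening "would further bring down the rate to 6" per cent), an absolute reduction of 3 points to 3%, 80% power and a 5% level (two-sided assumed).

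- Uncorrected formula: n = [1.960·√(2·0.045·0.955) + 0.842·√(0.06·0.94 + 0.03·0.97)]² / 0.03² = 749 per group.
- With the continuity correction, the usual approximation to Fisher's exact test: 814 per group, as stated.
- Attrition of 5%: 814/0.95 = 857 per group, 1714 in total, as stated.
- Exact power of Fisher's test at 814 per group: 80.9%.

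The sample size is sound and concerns preterm birth only. It is used below to fix the number of women per group, assuming 814 per group have both scans.

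**2. Precision for cervical length.** Let r be the within-group correlation between baseline and mid-trimester cervical length. In large samples,

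variance(ANCOVA) = (1 − r²) × variance(unadjusted difference in means).

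The confidence interval narrows by 1 − √(1 − r²). In SD units the unadjusted difference detectable with 80% power is (1.960 + 0.842)·√(2/814) = 0.139, which adjustment multiplies by √(1 − r²). The last column is the power of the adjusted analysis for a difference that the t test detects with 80% power.

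| Assumed r | Variance ratio | CI narrower by | Detectable difference (SD) | Power |
|---|---|---|---|---|
| 0.1 | 0.99 | 0.5% | 0.138 | 80.4% |
| 0.2 | 0.96 | 2.0% | 0.136 | 81.6% |
| 0.3 | 0.91 | 4.6% | 0.132 | 83.6% |
| 0.4 | 0.84 | 8.3% | 0.127 | 86.4% |
| 0.5 | 0.75 | 13.4% | 0.120 | 89.9% |
| 0.6 | 0.64 | 20.0% | 0.111 | 93.8% |

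The comparison is with the t test. If the plan's rule led to the Mann-Whitney test, the relative precision would also depend on the shape of the distribution, which the document does not describe.

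**3. Is chance imbalance a separate loss?** The standard error of the baseline difference between groups is √(2/814), about 0.05 SD. It carries into the outcome comparison multiplied by r: about 0.015 SD at r = 0.3 and 0.03 SD at r = 0.6. Its variance, r²·2/814, is exactly the share that adjustment removes in step 2. It is the same loss and must not be counted twice.

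**4. Does another stated analysis use the baseline?** The logistic model names the mid-trimester length. Its allowance for other risk factors, and an interaction sentence that does not say which scan it means, could admit the baseline length. The response would still be preterm birth, so neither would adjust the comparison of mid-trimester cervical length.

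**The case against.** The strongest reply has three parts.

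*The sentence is a general default in a condensed article, and covariate adjustment of one secondary outcome is usual SAP material.* This stands in part. The sentence does not mention cervical length, and an adjusted model is not expressly excluded. But it does name the tests for continuous data, and this outcome falls under them.

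*Nothing is wrong with the stated test.* This stands in full. A reader might infer that ignoring the baseline biases the comparison or inflates its type I error. It does neither: randomization protects the unadjusted comparison.

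*The practical gain may be small.* This stands for low correlations. At r of 0.1 to 0.2 the variance falls by only 1% to 4%, and a trial sized for 6% versus 3% already detects 0.139 SD in cervical length without adjustment. The gain becomes material from about r = 0.4 to 0.5.

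Two further inferences go beyond the document. A reader might call this the key mechanistic outcome. The document ranks it no higher than the other obstetric secondary outcomes, puts the mechanism forward only as one possibility, and confines its stated hypothesis to preterm birth. A reader might also blame the nearly six-week scan window for avoidable noise. The document gives no figure for how cervical length varies across that window, and gestation at scan is recorded after randomization.

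**Conclusion.** The point holds as a loss of efficiency in one secondary comparison. A pre-treatment measurement of the same variable is planned for every woman, and the stated analysis of the later measurement does not use it. For an assumed correlation of 0.1 to 0.6, the unadjusted analysis gives up 1% to 36% of the variance, and its confidence interval could be about 0.5% to 20% narrower. The result rests on that assumed range, on the large-sample ANCOVA formula and on about 814 women per group with both scans.

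It does not touch the primary outcome, its Fisher's exact test or the sample size. Serum progesterone is also measured repeatedly, and a reader might extend the point to it; no calculation here supports that extension, so it is not made. Severity is minor: a free improvement, not the correction of an error.

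**What to change.** Prespecify, in the protocol or the SAP, a linear model (ANCOVA) for cervical length at 18+0 to 23+6 weeks with treatment group and baseline cervical length as explanatory variables. Report the adjusted mean difference in millimetres with its 95% confidence interval, and keep the Mann-Whitney test as a sensitivity analysis. Adding gestational age at scan is optional and belongs only in a sensitivity analysis, because it is recorded after randomization.

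The wording should be fixed before any comparison of cervical length by group. The cost is one sentence and one extra model, with no new data, visits or participants.

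### The secondary logistic model adjusts the treatment effect for mid-trimester cervical length, a post-randomization measurement that treatment is hypothesized to change, and the interaction test appears to use it too

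*Protocol article*

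**What the plan says.** All references are to the protocol article.

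- **Primary analysis** (Analysis plan): an unadjusted Fisher's exact test to "compare the difference of PTB rates between the progesterone and control groups".
- **Logistic analysis** (Analysis plan): "Logistic regression analysis will be applied to evaluate the association between PTB and the effect of early universal use of progesterone", together with prior preterm birth, "cervical length measurement at 18 + 0 to 23 + 6 weeks of gestation, serum progesterone level, and other risk factors". The window of the cervical scan is fixed; the time point of the serum progesterone is not.
- **Interaction** (Analysis plan): "The interaction effect will be evaluated to assess the impact of the history of previous PTB or cervical length on treatment effect". This sentence does not say which cervical scan is meant. The sentence before it names only the mid-trimester one.
- **Timing** (Randomization and masking): allocation takes place "on the day of first TVCL measurement before 14 + 0 weeks of gestation". The Procedure section starts medication at 12+0 to 14+0 weeks.
- **Mechanism** (Background and rationale): "Early progesterone treatment may maintain uterine quiescence and prevent shortening of the cervix from early gestation".
- **Other uses of the scan:** Obstetric outcomes lists the mid-trimester cervical length as a secondary outcome. Under Procedure, a value of 25 mm or less leads to unblinding, and placebo women are then offered progesterone.
- **Baseline data:** cervical length (Abstract, Methods) and serum progesterone (Procedure) are both also measured at recruitment.

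**The concern.** A covariate in a model for a randomized treatment effect should be fixed before randomization. The mid-trimester cervical length is not. By the protocol's own account it may lie on the path from early progesterone to fewer preterm births. Holding it constant removes whatever part of the benefit passes through it. A treatment that worked by preserving the cervix could then be reported as having no independent effect, next to a primary test that shows a benefit.

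The interaction raises a related problem. If it uses the same scan, its subgroups are formed after treatment has begun. The women with a short cervix on progesterone need not be the same kind of women as those with a short cervix on placebo. The treatment contrast also changes at 25 mm, because placebo women below that limit are offered progesterone. The resulting statement about who benefits would not describe women as they present at recruitment, which is when a universal strategy has to be decided.

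**Working it through.** **1. The plan's own figure.** Inputs from Sample size estimation: 6% versus 3%, 5% level (taken as two-sided), 80% power, 5% attrition.

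- Uncorrected: n = [1.960·√(2·0.045·0.955) + 0.842·√(0.06·0.94 + 0.03·0.97)]² / 0.03² = (0.5746 + 0.2461)² / 0.0009 ≈ 748.4, so 749 per group.
- Continuity-corrected: (748.4/4)·[1 + √(1 + 4/(748.4·0.03))]² ≈ 813.7, so 814. Exact Fisher power at 814 per group is 80.9%.
- Attrition: 814/0.95 = 856.8, so 857 per group and 1714 in total.

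The stated size is reproduced. It contains no covariate, so nothing below changes it. The design effect as an odds ratio is (0.03/0.97)/(0.06/0.94) ≈ 0.48.

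**2. Timing of the covariate.** Shortest gap: 18+0 minus 14+0 = 4 weeks. Longest gap: 23+6 minus 12+0 = 11 weeks 6 days. The scan is post-randomization for every woman.

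**3. Illustration of the adjustment.** The documents give no effect of treatment on cervical length, so every value here is an assumption: 400,000 women per scenario; control risk about 6%; log odds ratio for preterm birth of −0.6 per SD of cervical length; treatment lengthens the cervix by 0 to 1.0 SD. Where a common cause is included, it has a loading of 0.6 on cervical length and its own log odds ratio of −0.6 for preterm birth. Entries are the treatment odds ratio, unadjusted → adjusted for mid-trimester length.

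| Shift (SD) | Only through cervix | Only through cervix, plus common cause | Direct log odds ratio −0.4, plus common cause |
|---|---|---|---|
| 0 | 1.00 → 1.00 | 1.02 → 1.02 | 0.68 → 0.66 |
| 0.25 | 0.85 → 0.99 | 0.87 → 1.09 | 0.60 → 0.73 |
| 0.5 | 0.76 → 1.02 | 0.76 → 1.20 | 0.51 → 0.80 |
| 1.0 | 0.55 → 0.99 | 0.56 → 1.39 | 0.39 → 0.95 |

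Simulation error on the log scale is about √(1/12,000 + 1/12,000) ≈ 0.013, from roughly 12,000 events per arm at 6%.

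- With no shift, adjustment changes almost nothing.
- With a shift and no common cause, the adjusted value correctly shows no direct effect, but that is a different question from the total effect.
- With a shift and a common cause, the adjusted value is not the direct effect either. The true direct odds ratio is 1 in the third column and exp(−0.4) = 0.67 in the fourth.
- The scenario closest to the design (6.0% versus 3.2%) is the fourth column at 0.5 SD: 0.51 → 0.80.

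**4. Interaction.** The linear interaction odds ratio stayed between 0.97 and 1.02 in all scenarios, so these runs show no numerical bias in it. They did not model the offer of progesterone to placebo women at 25 mm or less. The argument on the interaction is therefore structural. At the local 4.6% with a cervix below 25 mm (Sample size estimation), the stratum holds about 0.046 × 857 ≈ 39 women per arm, selected after randomization.

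**The case against.** **The analysis is secondary and hedged.** The covariate list reads "cervical length measurement at 18 + 0 to 23 + 6 weeks of gestation, serum progesterone level, and other risk factors, if appropriate", and the text speaks of association, which suits a risk-factor model. The first part stands and limits the severity. The prognostic reading does not remove the problem: treatment is in the model, and the next sentence interprets the treatment effect by cervical length.

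**Treating short-cervix placebo women is part of the design.** The control strategy in the Primary objective is screening of "cervical length at 18 + 0 to 23 + 6 weeks" with progesterone for those found short. This stands for the overall comparison. It does not turn a subgroup defined after randomization into a baseline characteristic.

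**The mechanism is only a hypothesis.** The Background offers it as one possibility, with uterine quiescence beside it. This stands: the bias is conditional, and full mediation is an extreme case.

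**Stronger readings that a reader might infer, and that the documents do not support:**
- *Serum progesterone is equally at fault.* No interaction with it is planned, and its time point is not given. The recruitment sample is a valid covariate; only the two later samples would share the problem.
- *The interaction is shown to be an artefact.* The scan it uses is not named, and no numerical bias was demonstrated.
- *The trial's main result is distorted.* A benefit acting through the cervix appears in full in the unadjusted Fisher's exact test.

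**Conclusion.** The point holds for the secondary logistic model and, if it uses the mid-trimester scan as the context suggests, for the cervical-length interaction. Should treatment change cervical length as the protocol hypothesizes, the adjusted odds ratio will not estimate the total effect of the early universal strategy. Under the assumed effects it moves toward 1, or past it when short cervix and preterm birth share an unmeasured cause. The size depends on values that the documents do not give, and the distortion essentially vanishes if treatment leaves the cervix unchanged. The interaction would compare subgroups formed after randomization and cannot be read as baseline effect modification. Severity: should-fix, confined to a secondary analysis.

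**What to change.** In the Analysis plan, restrict the treatment-effect logistic model and both interaction tests to variables fixed before randomization: cervical length at recruitment, serum progesterone at recruitment and prior preterm birth. State these time points explicitly. Compare the mid-trimester cervical length and the two later progesterone levels between groups as outcomes. If a model containing them is still wanted, label it as an exploratory prognostic or mediation analysis, and do not present its treatment coefficient as the effect of the strategy.

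The cost is a change of wording. Both baseline measurements are already scheduled at recruitment, and the sample size is untouched. The one drawback is that first-trimester cervical length may predict preterm birth less strongly than the later scan, so the adjusted model may gain less precision.

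### The half-way stopping rule uses the same P < 0.05 as the final test, so with Fisher's exact test the overall type I error is about 6.0–6.2%, not the stated 5%

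*Protocol article*

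**What the plan says.** All the relevant text is in the Statistics section of the protocol article.

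- **Primary test** (Analysis plan): "The primary analysis will be evaluated by Fisher’s exact test to compare the difference of PTB rates between the progesterone and control groups".
- **Threshold** (Analysis plan): a P "value < 0.05 will be considered as statistically significant". No other level appears anywhere.
- **Timing of the look** (Analysis plan, the next sentence): "Interim analysis will be done when the primary outcome is available for 850 subjects (~ 50% of the intended recruitment").
- **Consequence** (same sentence): "the trial will be stopped if there is a significant difference in the PTB rate between the two groups".
- **Design level** (Sample size estimation): "A sample size of 814 per group is required to achieve power of 80% power at the 5% significant level", for 6% in the control group and an absolute reduction of 3 points.
- **Recruitment** (Sample size estimation): "Assuming an attrition rate of 5%, a total of 1714 subjects (857 subjects per group) will be recruited".

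The article names no boundary, spending function or reduced final level. It does not restrict the stop to one direction.

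**The concern.** The stopping sentence directly follows the definition of significance. On a plain reading, P < 0.05 therefore ends the trial at 850 outcomes, and P < 0.05 also decides it at the end. A trial with no true effect then has two chances to be declared positive, each at the full level, while the sample size section claims 5% for one test.

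At stake is the error rate of the primary comparison, in a trial asking whether to treat all women with singleton pregnancies. The rule can also end the trial on few events: 26 v 13 is enough, 39 preterm births in total.

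**Working it through.** **Inputs.** From the article: 6% v 3%, 5% level, 80% power, 814 per group evaluable, 5% attrition, 1:1 allocation, Fisher's exact test, interim at 850 outcomes. Assumed: 425 per arm at the interim, and a two-sided test. Sidedness is not stated, but only a two-sided calculation gives 814; one-sided gives 590, or 655 with continuity correction.

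**1. Reproduce the plan's sample size.** With p̄ = 0.045,

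n = [1.96·√(2·0.045·0.955) + 0.842·√(0.06·0.94 + 0.03·0.97)]² / 0.03² = 748.4, rounded up to 749.

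With continuity correction, n/4·[1 + √(1 + 4/(n·0.03))]² = 813.7, rounded up to **814**. Then 814/0.95 = 856.8, so 857 per group and 1714 in total. Both figures reproduce as a single 5% test with no allowance for an interim look. Exact Fisher power at 814 per arm is 80.9%.

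**2. Information at the look.** 850/1714 = 49.6% of recruitment; 850/1628 = 52.2% of evaluable women.

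**3. Type I error of the rule as written.** Overall error = Pr(interim P < 0.05) + Pr(interim P ≥ 0.05 and final P < 0.05), by exact binomial enumeration with Fisher P values at 425, then 814 per arm:

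| Common rate | Interim | Final | Overall | One final test |
|---|---|---|---|---|
| 4.5% | 3.4% | 2.6% | 6.0% | 3.8% |
| 6% | 3.5% | 2.7% | 6.2% | 3.9% |

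Over common rates of 3% to 8%, with 814 or 857 per arm at the end, the overall figure runs from 5.7% to 6.6%. For comparison, a test that used its full nominal level would give 8.2% (bivariate normal, |z| > 1.96 at both looks, correlation √0.522).

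**4. What it takes to stop.** 26/425 v 13/425 (3.1 points) gives P = 0.048 and stops the trial; 26 v 14 gives P = 0.074 and does not. With fewer events a smaller gap is enough: 19 v 8 (2.6 points) gives P = 0.049.

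**5. Behaviour at 6% v 3%, 814 per arm at the end.** Type I error is at a common 6% rate.

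| Levels (interim / final) | Type I error | Power | Stops at interim | Mean observed reduction if stopped |
|---|---|---|---|---|
| As written: 0.05 / 0.05 | 6.2% | 82.6% | 50% | 4.1 points |
| O'Brien-Fleming type, 50% information: 0.0031 / 0.0490 | 3.9% | 80.9% | 16% | 5.1 points |
| Haybittle-Peto: 0.001 / 0.05 | 4.0% | 80.9% | 9% | 5.5 points |
| Pocock: 0.0294 / 0.0294 | 3.7% | 76.2% | 41% | 4.3 points |

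At 52.2% information the O'Brien-Fleming-type levels are 0.0038 / 0.0487. Error and power are practically the same, and the trial stops early 17% of the time.

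If the true reduction is only 2 points (an assumption: 6% v 4%), the rule as written stops for benefit 22% of the time, with a mean observed reduction of 4.0 points.

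**The case against.** The strongest reply is that the breach is small. Fisher's test is conservative at these event rates, so the excess over 5% is about 1 point two-sided, and the chance of falsely declaring benefit is about 3.1% (6.2%/2) against 2.5%. That stands, and it settles the size of the point. It does not remove it: the stated level is exceeded, and the error is more than half as large again as for one final Fisher test.

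A second reply is that the full protocol or a statistical analysis plan may contain a boundary. It may. But the article is not silent here: it fixes the timing, the consequence and the only meaning of significance. A boundary elsewhere would contradict this text and would not merely complete it.

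A reader might also infer more than the article supports:

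- **That the error rate is 8.2%.** That figure is for a test at its nominal level, not the planned Fisher test.
- **That a stricter boundary cures overestimation.** It does not. In a stopped trial the mean observed reduction rises from 4.1 to 5.1–5.5 points. The gain is that such stops become rarer. Averaged over all trials at 6% v 3%, the rule as written gives about 3.3 points against a true 3.0, so the overall bias is small.
- **That any stop needs a gap as large as the planned effect.** This fails at lower event counts, as 19 v 8 shows.
- **That half the neonatal and safety data would be lost.** Women already enrolled but not yet delivered would add to the 850. At the reported pace of 310 in about a year, with about six months from enrolment to outcome and recruitment not paused (an assumption), some 150 more would be in the trial. The shortfall is then (1714 − 1000)/1714, about 42%.

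**Conclusion.** The concern holds at a modest size. As written, the interim rule and the final test both use P < 0.05, and the sample size section's 5% level is not kept: the overall two-sided type I error is about 6.0% to 6.2% at a common rate of 4.5% to 6%. Under the planned effect the trial would end half-way about half the time, with an observed reduction averaging 4.1 points.

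This rests on reading the stopping sentence with the article's only definition of significance, on 425 per arm at the look and 814 at the end, and on a two-sided test. The type I error is the main point. Overestimation after an early stop is a reason to report an adjusted estimate; it does not by itself show that this boundary is worse than another.

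**What to change.** Replace the stopping sentence with a pre-specified group-sequential boundary, and state four things:

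1. **The levels.** For example, Lan-DeMets O'Brien-Fleming computed at the actual information fraction (about 0.003 to 0.004 at the interim, 0.049 at the end), or Haybittle-Peto (0.001 at the interim, about 0.05 at the end).
2. **The comparison.** The boundary applies to the intention-to-treat analysis only. The Analysis plan currently names intention-to-treat and per-protocol together as primary.
3. **The direction.** Say whether the same boundary governs an excess of preterm birth on treatment, since the present wording covers a difference either way.
4. **The estimate.** If the trial stops early, report an effect estimate and interval that account for the stopping rule.

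The cost is a few sentences. With either example, power at 6% v 3% stays at about 81% with 814 per arm, so 1714 women still suffice. A Pocock boundary would not be free: power falls to 76.2%. The real price is a lower chance of stopping early under the planned effect, about 16% or 9% instead of 50%. With 310 women recruited at the article's status date, the 850-outcome look was still well ahead, so as of this document the boundary could be set before any interim result.
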